### The trauma informed care (TIC) psychoeducational intervention for schools

2.1.

The SCS psychoeducational TIC school programme (Bath et al., 2021) provides a pedagogical framework for understanding how significant adults create conditions for healing and recovery in children who are exposed to trauma. With an aim of developing teachers’ ability to respond to pupils with a trauma-informed approach, the 5-day programme builds around the themes of safety, connections, and coping (Bath, 2015), and provides education about compassion fatigue and secondary traumatic stress, practical TIC training, and workshops on TIC implementation at an organisational level. TIC-ambassadors continue to work closely with the principal and support the TIC organisational implementation after finished training. For participation in the SCS-TIC programme, school principals must apply to the Swedish National Agency for Education, who then, based on the school’s written application and interviews with the school principal, select (prioritise) based on parameters including implementation capacity and the likely prevalence of trauma in the pupil population.

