### Participants and recruitment

2.3.

Participants will be teachers and other professionals in the school context (principals, special teachers, school nurses) working in Swedish schools, from primary school to high school. Participants in the experimental group (*N* = 160) will be recruited from schools who participate in the SCS-TIC training programme. Sixteen (16) training groups consisting of 35 people each participate in the SCS-TIC training programme each semester. Participants will be excluded if they do not complete the programme. An equally large control group (*N* = 160) will be recruited from schools not receiving the SCS-TIC programme. For recruitment, participants in the experimental group will be contacted through collaboration with SCS. Participants in the control group will be invited to the study through e-mail and targeted on social media platforms.

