### Data collection

2.4.

For data collection, we use a digital platform that sends invitations to participation and unique personalised links via email/SMS, allowing participants to respond in their own time, via smartphone, tablet or computer. Data is safely and reliably combined by the digital platform software, without personal codes or human handling, thereby maximising confidentiality and minimising risk of error. It will be possible for participants to listen to the survey questions and information about the study.

Given that the experimental group is determined by the standardised procedure of the Swedish National Agency for Education who handles the applications for participation in the SCS-TIC programme, it cannot be claimed that the experimental group is randomly selected. Nevertheless, although access to school (socioeconomic and ethnic) data is restricted by current state regulations, we strive to match the schools that contribute to the experimental group with schools of similar student population composition (class sizes, proportion of immigrant students), geographic location (i.e. urban or suburban-located schools), and socioeconomic status (i.e. location of the school) in the control group. Schools in the control group are randomly selected among those who match on the above criteria, based on a draw.

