### Power/sample size calculations, data analysis plan and attrition analyses

2.7.

A power analysis employing R and G*Power with an aimed .80 power, significance level of .05 and an effect size of *d* = .5, yielded a sufficient sample size of *N* = 99 for our basic analyses. Estimating a drop-rate of about 40% over time, perhaps even higher for the control group, we determined a target sample size of *N* = 160 for the experimental group and *N* = 160 for the control group.

Data from all measures will be analysed using R (R Core Team, 2021) and JAMOVI (The Jamovi Project, 2022). Attrition analyses will be conducted, and missing data among participants who have completed all four measurements will be handled either utilising multiple imputation or by applying maximum likelihood estimation when employing the mixed linear model analysis. Independent *t*-tests will assess potential differences between experiment and control group concerning outcome measurements (e.g. perceived teacher efficacy, classroom management strategies, burnout and compassion fatigue symptoms) at baseline. For hypothesis testing, we will employ mixed linear model analyses of repeated measures to estimate fixed (i.e. the trauma-informed care training) and random (e.g. participants’ social class, gender, ethnicity) effects of training on the study outcome variables, comparing both within individuals (repeated measures analysis) and between groups (experimental versus control group measures at each timepoint). Interaction factors in the models are used for estimating potential moderation by ethnicity, socioeconomic status and other characteristics. For example, a three-way interaction of gender, ethnicity and social-class may uncover intersectional outcomes particularly for women with non-Swedish backgrounds that might indicate a heightened trauma-informed care approach to vulnerable students independently of whether they are in the experimental or control group.

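### The random part of the mixed model is given as gender, ethnicity and social class, with no school or training-group term named, although exposure is set by school and delivered in groups

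*Protocol article*

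**What the plan says.** **Model.** Section 2.7 of the protocol article specifies mixed linear models for repeated measures. Training is the fixed effect, and the other component is "random (e.g. participants’ social class, gender, ethnicity) effects of training on the study outcome variables". The comparisons named are within individuals and between the two arms at each timepoint. The next sentence uses ethnicity, socioeconomic status and other characteristics as interaction factors to estimate moderation, and a gender by ethnicity by social-class interaction is given as an example.

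**Assignment and delivery.** Under section 2.1, principals apply on behalf of their schools and the national agency chooses among them. The programme includes "workshops on TIC implementation at an organisational level", and ambassadors go on working with the principal after training. Section 2.3 states: "Sixteen (16) training groups consisting of 35 people each participate in the SCS-TIC training programme each semester". For the controls, section 2.4 states: "Schools in the control group are randomly selected among those who match on the above criteria, based on a draw". The Discussion confirms that the allocation decision concerns schools.

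**Power.** Section 2.7 works "with an aimed .80 power, significance level of .05 and an effect size of *d* = .5", which "yielded a sufficient sample size of *N* = 99 for our basic analyses". It then allows for loss ("Estimating a drop-rate of about 40% over time, perhaps even higher for the control group") and sets "a target sample size of *N* = 160 for the experimental group and *N* = 160 for the control group". The article mentions no ICC, design effect or cluster-robust variance.

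**The concern.** Two separate things are wrong with the stated random part.

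First, it omits the level at which exposure is assigned. Colleagues share a school, a training group and an implementation process, so their answers may be correlated. A model whose only levels are the individual and the arm treats them as independent. Comparisons of the arms at a timepoint then have confidence intervals that are too narrow and too many false positives. Hypotheses H1 to H4 are tested through this model.

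Second, it includes factors that do not belong there. Gender, ethnicity and social class have few levels, and those levels are of interest in themselves. A variance component for gender is barely estimable. The same section wants the effects of these factors as moderators, which is a fixed-effect question. The two sentences give the same factors incompatible roles.

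**Working it through.** **1. The plan's own sample size.** Inputs from section 2.7: power .80, alpha .05 (sidedness not stated), d = .5.
- One-sided, independent participants: total N = 4 × ((1.645 + 0.842)/0.5)² ≈ 98.9. This matches 99, as a total over both arms.
- Two-sided: 2 × ((1.960 + 0.842)/0.5)² ≈ 62.8, so 63 per arm (64 by t-test), or 126 to 128 in total. This does not match 99.

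The only match found with the stated inputs is a formula for independent participants.

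**2. Analysed number.** 160 × (1 − .40) = 96 per arm. If these were independent, two-sided power at d = .5 would be Φ(0.5/√(2/96) − 1.96) = .93.

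**3. Assumptions.** The documents give neither an ICC nor the number of clusters. I take an ICC of .02 to .10 and 10 or 16 clusters per arm. Sixteen is the number of training groups in one semester.

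**4. Formulas for a comparison of arms at one timepoint.** With k clusters per arm:
- m = 96/k
- design effect DE = 1 + (m − 1) × ICC
- true SE divided by naive SE = √DE
- actual type I error of the naive 5% test = 2 × (1 − Φ(1.96/√DE))
- power of a correct analysis: noncentral t with 2k − 2 degrees of freedom and noncentrality 0.5/√(2 × DE/96)

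| k per arm | m | ICC | DE | SE ratio | Type I error | Power |
|---|---|---|---|---|---|---|
| 16 | 6 | .02 | 1.10 | 1.05 | 6.2% | .89 |
| 16 | 6 | .05 | 1.25 | 1.12 | 8.0% | .85 |
| 16 | 6 | .10 | 1.50 | 1.22 | 11.0% | .78 |
| 10 | 9.6 | .02 | 1.17 | 1.08 | 7.0% | .86 |
| 10 | 9.6 | .05 | 1.43 | 1.20 | 10.1% | .78 |
| 10 | 9.6 | .10 | 1.86 | 1.36 | 15.1% | .67 |

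A simulation with 16 clusters of 6 per arm (4,000 runs per setting) gave 6.3%, 7.9% and 10.5% for the naive test at the three ICCs, and about 5% for a test on cluster means.

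**5. Clustering in the trained arm only.** The variance inflation is then (1 + DE)/2. At k = 16 and ICC .02 it is 1.05, with type I error 5.6%. At k = 10 and ICC .10 it is 1.43, with type I error 10.1%.

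**6. Change from baseline.** A stable school effect cancels when baseline is subtracted, so the ICC of the change score is 0 and DE = 1. Simulation with stable school effects only gave about 5% (4.7% to 5.9% over 5 to 16 clusters per arm). If school or group effects shift over time, the formulas in step 4 apply with the ICC of the change score in place of the cross-sectional ICC. The documents do not let one say how large that is.

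**The case against.** **The list is illustrative.** It opens with e.g., and this is a condensed article whose full random structure may be set out in an analysis plan. It does not even name a participant intercept, although repeated measures are declared. This stands in part: school is unnamed, not excluded. A reader might infer that the authors have decided to ignore clustering, and the text does not show that. But the article does state what the random part is made of. Every example is a participant characteristic, and the sample size fits independent participants.

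**Moderation is handled by interactions.** This stands. A reader might infer that the trial relies on random effects to estimate moderation. Section 2.7 says otherwise in the next sentence. What remains is a wrong label that conflicts with that sentence.

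**H1 to H4 concern change after training.** This also stands in part. Stable school differences do not inflate a change contrast. But arm comparisons at each timepoint are planned too, and shared training and school-wide implementation could produce correlated change.

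**Controls may be less clustered.** Section 2.3 recruits them by e-mail and social media. This reduces the size of the error, as step 5 shows.

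**Larger figures could be quoted.** With 5 clusters per arm and ICC .10, DE = 1 + 18.2 × .10 = 2.82, type I error is 24% and power .44. If the clusters are training groups, that needs 160/5 = 32 of 35 trainees in each group to enrol, plus equal clustering among controls. Under the same setting with only the trained arm clustered, type I error is about 16%. I do not rest the point on that case.

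**160 per arm leaves slack.** It protects power: at DE 1.50 power is still .78. It does not correct the standard errors.

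**Conclusion.** The point holds in conditional form. Run as described, the model ignores the level at which exposure is assigned and delivered. If the ICC within school or training group is positive, it understates the standard errors of the arm comparisons at each timepoint. With 96 analysed per arm, 10 to 16 equally clustered clusters per arm and ICCs of .02 to .10, type I error is about 6% to 15% instead of 5%. With clustering in the trained arm only it is about 6% to 10%. The ICCs, the cluster counts and the equal clustering are assumptions.

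One cannot conclude that every standard error in the trial will be too small: change-from-baseline contrasts are affected only if school or group effects vary over time. Labelling gender, ethnicity and social class as random is wrong whatever the ICC, because the same section tests them as moderators.

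**What to change.** - State random effects for participant and for school and/or training group. Include a school-by-time (or group-by-time) term, or use cluster-robust variance with a small-sample correction. Random intercepts alone would not remove inflation caused by cluster effects that change over time.
- Enter gender, ethnicity and social class, with their interactions with training and time, as fixed effects.
- Keep a school and a training-group identifier in the data. Section 2.4 describes data combined without personal codes and section 3.1 promises prompt anonymisation, so the identifiers must be attached before that step or they may be lost.
- Restate power with a design effect over a stated ICC range, and say whether 99 is a total or a per-arm number and whether the test is one- or two-sided.

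The cost is revised model wording, two identifier fields arranged before anonymisation, somewhat wider confidence intervals and a lower stated power. In the table above, power falls from .93 to between .89 and .67.

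### In a non-randomised comparison, section 2.7 names follow-up arm differences and within-person change as the hypothesis tests, but not the between-arm difference in change from baseline

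*Protocol article*

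**What the plan says.** Section 2.4 concedes that "it cannot be claimed that the experimental group is randomly selected". Section 2.1 explains why: principals apply, and the agency prioritises schools partly on capacity to implement and on expected trauma among pupils. Section 2.3 recruits trained participants through the programme provider and controls by e-mail and social media. Section 2.4 adds that the authors try to match control schools on pupil composition, location and socioeconomic position, under restricted access to school data.

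Section 2.7 fixes three things that matter here.

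- Independent t-tests "will assess potential differences between experiment and control group concerning outcome measurements" at baseline. Nothing is said about what follows from them.
- Hypotheses are tested in a repeated-measures mixed model, "comparing both within individuals (repeated measures analysis) and between groups (experimental versus control group measures at each timepoint". Training is the fixed effect. Social class, gender and ethnicity are given as examples of random effects.
- Interaction factors are to estimate moderation by ethnicity, socioeconomic status and other characteristics. The one example is gender by ethnicity by social class, which might show "a heightened trauma-informed care approach to vulnerable students independently of whether they are in the experimental or control group".

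**The concern.** The way schools enter the programme makes baseline differences likely, and attempted matching on pupil and area characteristics does not cover motivation, capacity to implement or the two recruitment routes. Of the two comparisons named for hypothesis testing, the arm difference at T2, T3 or T4 includes whatever difference existed before training. Change within the trained arm removes each person's stable level but keeps any trend over the school year and any regression to the mean. Each comparison lacks what the other provides. The between-arm difference in change from T1 combines them, and the text does not say that this is the training effect.

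The moderation example has a related gap. An interaction of three teacher characteristics, read regardless of arm, describes how teachers differ. It says nothing about whether the effect of training differs between them, although the abstract and conclusion hope to learn whether effects are independent of social category.

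At stake is the central causal claim: a difference between applying and non-applying schools could be read as a training effect.

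**Working it through.** **Inputs from section 2.7:** the power analysis was run "with an aimed .80 power, significance level of .05 and an effect size of" d = .5 and gave N = 99; sidedness is not stated. The target is 160 per arm with about 40% loss, so 160 x 0.6 = 96 completers per arm.

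**Assumptions, not in the document:** SD 1 at each timepoint; baseline arm difference b; correlation r between T1 and follow-up; two-sided 5% tests; normal approximation; participants independent, so clustering in schools is ignored.

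1. *The plan's own figure.* 4(1.6449 + 0.8416)^2 / 0.5^2 = 98.9, so 99 reproduces as a one-sided total over both arms. Two-sided, the answer is 63 per arm, 126 in total. Nothing below depends on this.

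2. *Follow-up arm contrast, no training effect, b stable.* SE = sqrt(2/96) = 0.144. Rejection rate = Phi(b/SE - 1.96) + Phi(-b/SE - 1.96).
   - b = 0.1: 10.7%
   - b = 0.2: b/SE = 1.39, giving 28.3%
   - b = 0.3: b/SE = 2.08, giving 54.7% (54.1% in 10,000 simulated trials at r = .6)

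3. *Difference in change from T1, same setting.* Its expectation is b - b = 0, so it rejects in 5% of trials whatever b is (5.3% in the simulation). SE = sqrt(2/96) x sqrt(2(1 - r)). Power for a true effect of 0.5:
   - r = .3: SE 0.171, power 83%
   - r = .5: SE 0.144, power 93%
   - r = .7: SE 0.112, power 99%

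4. *Change within the trained arm.* SE = sqrt(2(1 - r)/96). A drift of 0.2 SD shared by both arms is significant in 50% of trials at r = .5 (SE 0.102) and in 72% at r = .7 (SE 0.079), with no training effect.

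5. *Baseline t-test with all 160 per arm.* SE = sqrt(2/160) = 0.112. Power is 43% at 0.2 SD and 76.5% at 0.3 SD, so such differences go undetected in 57% and about 23% of trials. A non-significant result is weak reassurance.

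6. *If the baseline difference is not stable.* Suppose b = 0.2 shrinks to b x r, with r = .6 to .8.
   - The follow-up difference is 0.12 to 0.16 SD, and the follow-up contrast rejects in 13% to 20% of trials at 96 per arm.
   - The difference in change is then biased by -b(1 - r), that is -0.08 to -0.04 SD, and rejects in about 10% to 7%.

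   Conversely, if b is stable and baseline is entered as a covariate instead, b(1 - r) remains. For b = 0.3 and r = .5 to .7 that is 0.15 to 0.09 SD, with 22% to 14% false positives.

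7. *Moderation.* Assume a 20% minority share in each arm: 19.2 and 76.8 of 96. At one timepoint the SE of the group-by-moderator effect is sqrt(2/19.2 + 2/76.8) = 0.361. For change from T1, multiply by sqrt(2(1 - r)): 0.323 at r = .6 and 0.228 at r = .8. With the multiplier 2.80 for 80% power, the detectable difference in training effect is 0.90 to 0.64 SD, larger than the planned main effect of 0.5.

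**The case against.** It can fairly be said that the sentence in section 2.7 is shorthand for an ordinary between-within design. T1 is one of the four timepoints (section 2.2), so the planned model can deliver the contrast against T1. H1 and H3 in section 1.4 are worded as change. An article may leave exact contrasts and covariates to the analysis plan or preregistration. Non-randomisation is openly acknowledged and matching is attempted.

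Much of this stands, and it limits what may be inferred.

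- A reader might infer that the analysis will present selection as a training effect. The text does not say that a raw follow-up difference will be so read. It fails to commit to the contrast that would prevent it.
- A reader might infer that none of the named comparisons deals with baseline differences. Within-person change does remove stable personal levels; its weakness is time trend.
- A reader might infer that background variables will never adjust anything. A model with moderators would normally include their main effects. What is missing is their stated role as fixed adjustment terms.
- A reader might infer that no training-by-moderator term is planned. The general sentence on interaction factors leaves room for one; only the worked example lacks it. Section 1.4 makes no prediction on how training affects awareness of intersectional aspects.

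What does not stand is the plea of mere brevity. Section 2.7 goes beyond leaving detail open: it states which comparisons serve hypothesis testing, and neither, taken alone, isolates the training effect in this design.

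**Conclusion.** The point holds as a fault in the stated contrasts, not as proof that the analysis will be confounded. Followed as written, the follow-up arm contrast has a false-positive rate of 28% at a stable 0.2 SD baseline difference and 55% at 0.3 SD with 96 per arm, against 5% for the difference in change.

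These sizes rest on an assumed baseline difference that persists unchanged. If it shrinks over time, the gap narrows (13-20% against 7-10% at 0.2 SD) and the difference in change is itself slightly biased. It rests on parallel trends and does not remove all confounding. Matching, where achieved, would lower all these figures.

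On moderation, the three-way example is not evidence about the intervention. Because only large differences in effect are detectable, a non-significant interaction would not show that effects are independent of social category.

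**What to change.** State in section 2.7, before analysis:

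- The training effect is the group-by-time contrast, that is, the difference between arms in change from T1 to T2, T3 and T4.
- The participant background variables of section 2.6 enter as fixed effects, together with any school matching variables actually obtained. Section 2.4 says access to school data is restricted, so not all may be available.
- The contrast assumes parallel trends in the absence of training.
- Standardised baseline differences are reported in place of baseline t-tests.
- Moderation is tested as group x time x moderator, one moderator at a time, as exploratory, with confidence intervals. Non-significance is not read as independence of social category.
- The gender by ethnicity by social class term, if kept, is presented as a description of teachers.

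The cost is wording, a few degrees of freedom and weaker moderation claims. The planned sample need not grow: the difference in change keeps 83-99% power for d = .5 at 96 per arm under the assumptions shown.

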## Abstract

**Background:** Adverse childhood experiences (ACE) can have negative effects on cognitive, social and emotion regulation abilities, which can threaten the child’s school integration and capacity to learn. While steady relations to sensitive, understanding adults may moderate these negative outcomes, the difficulties of children with ACEs pose a major challenge for teachers, whose insufficient preparation may lead to career attrition.

**Objective:** Psychoeducational trauma-informed care (TIC) interventions targeting teachers may strengthen teacher preparation and buffer the deleterious outcomes of ACEs, yet the evidence-base for these interventions is limited. Importantly, while minority groups are overrepresented among those with ACEs and additionally risk exposure to ethno-racial trauma, TIC interventions lack a social disadvantage/discrimination perspective. The Present trial addresses these issues.

**Method:** The study protocol employs a quasi-experimental design for assessing effects of a psychoeducational TIC intervention carried out in Swedish schools by Save the Children, Sweden (SCS). We compare, for the first time, an intervention group (*N* = 160) and a control group (*N* = 160) over time (pre-intervention, immediately after, 6 and 12 months post-intervention), assessing teacher stress, compassion fatigue, self-efficacy and trauma-informed knowledge. We monitor teacher attitudes and attributions of students’ academic weaknesses and behavioural and mental difficulties. The trial is preregistered (DOI:10.17605/OSF.IO/V7SH8).

**Results:** We hope that the mitigating effects of the SCS-TIC school intervention may be independent of social category, and that the trial will additionally generate knowledge of how providers and recipients of TIC may respond to it differently depending on their social and cultural identities. As school-based TIC practices and interventions are expansively relied on as means of preventing teacher burnout and career attrition, and buffering negative consequences of ACEs for children, establishing their effects with methodological robustness is important and timely.

**Conclusion:** Such knowledge may be used to tailor and target interventions to specific populations, while ensuring maximum effectiveness.

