### Aims and objectives of the planned study

1.4.

Despite paucity of empirical evidence of the effectiveness of TIC interventions, clinical research data indicate that an increased knowledge among caregivers concerning trauma and TIC practices leads to changed TIC attitudes (Brown et al., 2012). A recent meta-analysis of TIC interventions within the child welfare system indicated that caregivers reported reduced child PTSD symptoms and behavioural problems but only moderate improvement on children’s wellbeing (Zhang et al., 2021). However, while recent international studies regarding trauma-focused interventions are encouraging (Angelöw et al., 2023; Izzo et al., 2016; Purvis et al., 2015), most evaluations of TIC interventions suffer from methodological shortcomings and lack robust methods such as a control group or longer-term follow ups (Fondren et al., 2020; Hanson & Lang, 2016). In a school setting, the Three pillars intervention directed at teachers (Bath et al., 2021) has never been evaluated.

Therefore, the purpose of this study is to assess the effect of psychoeducational interventions in trauma-informed care directed at teachers. Building on the limited existing empirical evidence (MacLochlainn et al., 2022; Zhang et al., 2021) we expect that, after training in TIC, participants will report changed attitudes toward trauma-informed care and related practices (H1). These effects will be associated with increased perceived teacher efficacy, classroom management strategies (H2). Moreover, we expect decreased reported burnout and compassion fatigue symptoms (H3). Finally, we expect that these effects will be present also 6-months post-training (H4). Due to the underexplored nature of psychoeducational TIC interventions in terms of interactions with awareness about ethno-racial trauma and community specific experiences of ACEs, we refrain from making predictions concerning how the intervention might influence awareness about such socioeconomic and intersectional aspects of ACEs and trauma.

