### Study design

2.2.

We employ a quasi-experimental design with four measurements: Pre-training baseline (T1), directly after termination of training (T2), six months (T3) and twelve months (T4) after baseline. An experimental group (training in SCS TIC-programme) will be compared to a control group (no training in SCS TIC-programme). Participants in the control group will receive the same questionnaires with the same time interval between the measurement occasions.

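### Section 2.7 compares the groups at every wave without saying which wave and which group-by-time contrast decides H1–H3, and the 12-month wave belongs to no hypothesis

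*Protocol article*

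**What the plan says.** **Waves.** Section 2.2 sets a pre-training baseline (T1) and three later measurements: "directly after termination of training (T2), six months (T3) and twelve months (T4) after baseline". The abstract dates the later waves differently: "pre-intervention, immediately after, 6 and 12 months post-intervention".

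**Hypotheses.** Section 1.4 places H1 (changed attitudes) after training without a wave label. H2 (efficacy, classroom management) is tied to the H1 effects and H3 (burnout, compassion fatigue) stands alone; neither has a time. H4 reads "Finally, we expect that these effects will be present also 6-months post-training (H4"). Twelve months appears in none of the four.

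**Analysis.** Section 2.7 tests the hypotheses with a repeated-measures mixed model, "comparing both within individuals (repeated measures analysis) and between groups (experimental versus control group measures at each timepoint"). The only interaction terms it mentions are for moderation by ethnicity, socioeconomic status and similar characteristics. It names no deciding wave, no group-by-time contrast and no order of testing.

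**Alpha.** The .05 level appears only as an input to the power calculation ("with an aimed .80 power, significance level of .05 and an effect size of" *d* = .5), and that calculation is tied to no wave.

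**The concern.** The timepoint that decides a hypothesis is a protocol-level choice. The article is not silent here: it states a testing rule, and that rule spans all waves. Followed as written, it lets a difference at T2, T3 or T4 be offered in support of H1, H2 or H3.

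The choice can change the conclusion. Knowledge and attitudes could rise at T2 and fade by T4, while burnout might move only later.

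A second matter is what is compared. Sections 2.4 and 3 acknowledge that allocation is not random. A between-group difference at a given wave then mixes any training effect with whatever difference existed beforehand. The contrast that removes a stable pre-existing difference, change from baseline compared between groups, is not named as the deciding quantity.

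**Working it through.** **1. The plan's own figure.** Section 2.7 says the power analysis "yielded a sufficient sample size of" *N* = 99. For two equal groups, total = 2 × 2(z₁₋α + z₀.₈₀)²/d².
- One-sided .05: 4 × (1.645 + 0.842)²/0.25 = 98.9, which matches 99 as a total.
- Two-sided .05: 4 × (1.960 + 0.842)²/0.25 = 125.6, or 126, which does not match.

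The article states neither sidedness nor whether 99 is a total or per group. For this point, what matters is that 99 matches one comparison at one alpha, with no allowance for several waves.

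**2. Hypotheses against waves.**

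| Hypothesis | Time stated | Wave implied | Wave fixed in 2.7 |
|---|---|---|---|
| H1 | after training | T2 | none |
| H2 | none (tied to H1) | T2 | none |
| H3 | none | T2, by H4's back-reference | none |
| H4 | six months post-training, as persistence | T3 | none |
| – | twelve months | T4, no hypothesis | compared all the same |

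**3. Error on the implied reading.** One wave per hypothesis gives .05 per outcome and hypothesis. There is no inflation across waves.

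**4. Error if any wave counts.** Inputs: three tests per outcome, each at two-sided .05 (assumed, since 2.7 gives no level for wave-specific tests), and an equal correlation r between the wave statistics (assumed; not in the document). At r = 0 the rate is 1 − 0.95³ = 0.143. For r > 0 it was simulated with 2,000,000 trivariate normal draws.

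| r | P(at least one of T2, T3, T4 significant, no true effect) |
|---|---|
| 0 | 0.143 |
| 0.3 | 0.136 |
| 0.5 | 0.125 |
| 0.7 | 0.109 |
| 0.9 | 0.083 |

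This is 0.083/0.05 = 1.7 to 0.143/0.05 = 2.9 times nominal. Because H2 and H3 are directional, the favourable direction alone is also relevant: 0.042 (r = 0.9) to 0.073 (r = 0) against 0.025, much the same relative inflation.

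**5. T3 significant without T2, no true effect.** At r = 0 this is 0.05 × 0.95 = 0.0475; the simulation gives 0.020 at r = 0.9.

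**6. Baseline differences.** Let the pre-existing group difference be b and the training effect at wave t be δₜ. The difference at wave t estimates b + δₜ. The group-by-time contrast from T1 to wave t estimates (b + δₜ) − b = δₜ, provided b is stable over time.

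**The case against.** Three objections carry weight.

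*The wave is implied.* H1 speaks of the period after training, T2 falls directly after training, and H4 adds six months as a separate, later claim. That places H1–H3 at T2 and H4 at T3. This is the natural reading, and on it the 0.08 to 0.14 range applies to no hypothesis. But T3 and T4 also lie after training, and section 2.7 does not adopt the reading.

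*A mixed model can supply a single group-by-time test.* It can. Three freely chosen tests are permitted by the wording, not prescribed by it. The article simply does not say which test decides.

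*An analysis plan or the preregistration may settle this.* It may; neither is shown. Order of testing and the status of T4 are often set there. The published rule would still have to agree with them, and the deciding timepoint belongs in the protocol.

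A reader might also infer that H4 could be confirmed by a T3 difference with no initial effect, or that the plan tests T3 in isolation at .05. The documents do not support this. H4 refers back to the earlier effects and asks that they still be present, so a T3-only difference would not satisfy it as worded. Section 2.7 prescribes no order and no wave-specific level. What remains is that no rule in the analysis enforces the condition H4 contains.

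**Conclusion.** The point holds as a gap between the hypotheses and the stated analysis. The hypotheses imply T2 for H1–H3 and persistence at the six-month wave for H4. The analysis compares the groups at all waves, names no deciding group-by-time contrast, and includes a 12-month wave that serves no hypothesis.

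The size depends on the reading. It is .05 per hypothesis if the implied reading is followed, and about 0.08 to 0.14 per outcome if a difference at any of the three waves is accepted. The range rests on two-sided .05 at each wave and an assumed equal correlation of 0.9 to 0. It concerns waves within one outcome and would arise even with a single primary instrument.

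Which measurement decides H4 also has to be inferred, because the later waves are dated from baseline in section 2.2, from the intervention in the abstract, and from training in H4. These passages need to be reconciled.

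This should be corrected before analysis; it does not undermine the design.

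**What to change.** In sections 1.4 and 2.7, and in the preregistration if it does not already say so, state that:

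- H1–H3 are decided by the baseline-to-T2 group-by-time contrast from the planned mixed model;
- H4 is decided by the baseline-to-T3 contrast, tested only for outcomes that succeeded at T2, as its wording already implies;
- T4 is reported as an estimate with a 95% CI, outside the confirmatory tests;
- T3 and T4 are dated from the same origin throughout.

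Testing T3 only after success at T2 keeps the rate at .05 per outcome over the two steps, with no loss of alpha at T2. By comparison, a Bonferroni split over three waves (.05/3 = .0167) would need 84 per group at *d* = .5. With the stated 40% loss, 160 × 0.6 = 96 per group remain, and power at *d* = .5 would be 0.86 rather than 0.93 (two-sided, ignoring clustering).

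The cost is a few sentences and no new data. The downside is real: an effect that appears only at a later wave, for example in burnout, could be reported only as exploratory. If the investigators expect a late effect for a given outcome, another single contrast, such as an overall group-by-time test or an average over waves, would also control the error, provided it is named in advance.
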